### In situ organ reconditioning

To reverse or diminish the injury, many cytoprotective strategies have been tested in experimental models of transplantation and several have been shown to have therapeutic potential, including gene therapy,^18 19^ cytokine or growth factor administration,^20–22^ vasodilating agents and ischaemic preconditioning.^23 24^ Treatment of the organ during preservation has major logistic and ethical advantages over any attempt to achieve the same effects by treating the donor (therapeutic interventions before declaration of death are not currently permitted unless they are of potential benefit to the donor). Recently, there has been published early experience with normothermic regional perfusion of DCD donors, nevertheless the feasibility and benefit of this experimental approach is yet to be shown.^25^

### Normothermic machine perfusion of the liver

Bretschneider and Starzl first attempted machine perfusion of the liver in the late 1960s. Although hypothermic machine perfusion (HMP) has been shown some promise in clinical studies, normothermic machine perfusion of the liver (NMP-L) combats the limitations of SCS previously described by aiming to maintain the organ at the body’s natural temperature while providing oxygen, nutrition and the essential substrates necessary for adequate cellular metabolism. Providing a homeostatic environment theoretically enables us to extend our storage period and test the organs physiological parameters. To date, only one clinical trial of 20 adult recipients of livers maintained by HMP has been published showing a reduction in early graft dysfunction (5% vs 25% p<0.08) as well as a significant reduction in serum injury markers in the HMP group. A joint pilot trial between Oxford University, King’s College Hospital London and University Hospitals Birmingham Foundation Trust (UHBFT) recruited 20 patients into an NMP-L phase I study and concluded the procedure was feasible and safe when used on current conventional donor acceptance criteria.^26^ Following this, a 220-patient phase III international clinical trial entitled ‘consortium for organ preservation in Europe (COPE) work package 2 (WP2)’ has completed recruitment and the results are eagerly awaited. The Liver Unit at University Hospital Birmingham NHS Foundation Trust contributed to this multicentre international trial by randomising 50% of the study patients.

Our group believes NMP-L enables the donor organ to be functionally assessed, thereby increasing transplant safety. It can also extend organ preservation times to improve transplant logistics and donor organ use. There are several devices available on the market, but only the OrganOx metra has been widely used in the clinical transplant setting.^26^ Our team has performed over 70 liver transplants with grafts preserved on this machine and has gained broad experience by using this device. The OrganOx metra is the leading device in terms of the number of clinical transplants undertaken, with more than 100 machine-perfused livers transplanted in the phase III randomised European trial, together with 20 livers in the phase I safety study and further ongoing trials in North America. For these reasons, we have decided to use the OrganOx metra device for the proposed study.

The device consists of a unit that cradles the liver, a perfusate reservoir, oxygenators, pumps operating at physiological pressures and a closed tubing system that connects the unit to the portal vein, hepatic artery and vena cava. The constituents of the perfusate can vary but generally consist of whole blood for oxygen carriage, sources of nutrition (glucose, insulin, amino acids), antithrombotic agents (heparin, epoprostenol), antibiotics and acid-base agents which help reduce cellular oedema, cholestasis, microvascular injury and the effects of free radicals.

### Benefits of NMP-L

NMP-L does not simply benefit marginal DCD organs that have been exposed to a damaging FWIT. DBD is a catastrophic physiological event associated with profound hypotension (parasympathetic response) followed by hypertension, tachycardia and high levels of circulating catecholamines (sympathetic surge) followed by another reduction in the sympathetic outflow. These dramatic swings can cause significant graft ischaemia prior to retrieval. Diabetes insipidus occurs in 70%–80% of brain dead patients causing severe hypernatraemia (associated with primary liver graft non-function), hypokalaemia, hypocalcaemia, hypophosphataemia and hypomagnesaemia.^27 28^ Pirenne *et al* described seven cases when livers from DBDs between 70 and 80 years old were used with ‘favourable outcomes’.^29^ More recently, groups from Italy have reported excellent outcomes using grafts from octogenarian donors.^30 31^ NMP-L could however play an important role in preconditioning and assessing such organs prior to transplantation.

Hellinger *et al* were unable to identify a benefit using NMP-L in 1997; however, it was the first study of its kind.^32^ In 2001, Schon used NMP-L to preserve and recondition livers that had been exposed to 1 hour of warm ischaemia. These livers were then transplanted into pigs which all survived longer than 7 days. The group that received livers preserved using SCS had no survivors.^33^ Several studies have been published by the Oxford group, responsible for OrganOx metra. Imber *et al* published results from a study on a porcine model comparing NMP-L with SCS controls. They showed livers preserved using NMP-L were significantly superior (p<0.05) to SCS livers ‘in terms of bile production, factor V production, glucose metabolism and galactose clearance’, while SCS livers had higher perfusate levels of hepatocellular enzymes and more cellular damage.^34^ The same year, they successfully perfused and maintained five porcine livers for 72 hours, managing to maintain normal physiological parameters, pH, protein synthesis and histological architecture.^35^ In 2009, Brockman *et al* simulated DBD and DCD scenarios in a porcine model. After 5 hours of preservation (NMP-L vs SCS), there was no difference seen in preservation method in either the DCD or DBD graft recipients. After 20 hours of preservation, however, both DCD and DBD grafts that had been preserved using NMP-L were superior to their SCS counterparts with respect to enzyme release, histological changes and recipient survival. Of note, there was no difference in survival between DCD and DBD NMP-L-preserved graft recipients (83% and 86%, respectively).^36^

### Preclinical research and pilot study

Our team’s preclinical research on rejected human livers has demonstrated that metabolism of lactate, in combination with bile production, maintenance of physiological pH and stable blood flow rates are sensitive parameters predictive of organ viability. In April 2014, the UHBFT Novel Therapeutics Committee approved a pilot clinical project for transplantation of five reconditioned liver grafts, initially deemed unusable for transplantation. In this series, livers were declined by all the UK transplant units, after which NMP-L commenced following a variable period of SCS. Still, five out of six tested livers met the viability criteria and were successfully transplanted.^37^ Although this pilot project showed that viability testing has the potential to transform the organ selection and acceptance process of high-risk livers, our observation primarily provided the feasibility and short-term outcome data. In addition, this cohort also demonstrated the feasibility of performing NMP-L within a ‘back-to-base’ model, that is, following SCS and inspection at the transplant centre. This offers logistical and financial advantages over using NMP-L in place of SCS and may target livers that would benefit the most from NMP-L. More research in this area is required, and this was recognised by the Health Innovation Challenge Committee of the Wellcome Trust who awarded our study group a research grant to fund this trial. We have demonstrated so far that a proportion of currently rejected liver allografts might be salvaged by subjecting them to NMP-L and viability testing. Use of this technology could transform the use of high-risk organs and may improve access to treatment for thousands of patients awaiting liver transplantation globally.

## Methods

### Study design overview

Viability testing and transplantation of marginal livers (VITTAL) is an open-label, non-randomised, prospective, single-arm trial, using NMP-L testing viability and transplantation of marginal livers. It is being conducted at a single site (UHBFT). The design uses two linked components assessing: (1) the feasibility of NMP-L as a technique to increase the number of transplantable livers and (2) achievement of successful transplantation of the NMP-L treated marginal livers. (1) uses a two-stage adaptive design,^38^ requiring up to 53 marginal livers to be perfused. (2) uses a three-stage adaptive design^39^ and requires 22 NMP-L treated marginal livers to be transplanted. Success is measured by a 90-day patient survival—a nationally accepted, monitored and continually audited outcome following liver transplantation.

### Ethical and regulatory approval

The National Research Ethics Service (NRES) London-Dulwich (REC reference 16/LO/1056, Protocol number RG 15–240) and the Medicines and Healthcare Products Regulatory Agency (MHRA) approved all versions of the study protocol. This trial will use the OrganOx metra device following a variable period of SCS to evaluate organ viability pretransplant procedure. The OrganOx metra device currently has a Conformité Européene (CE) mark for liver organ transport and not organ evaluation. The use of the device within this clinical trial is therefore off registration and UK Competent authority (MHRA) clinical trial Investigation: No Objection was obtained (MHRA ref: CI/2016/0031. In addition, approval from the Research and Development (R&D) department at UHBFT and from National Health Service Blood and Transfusion (NHSBT’s) Research, Innovation and Novel Technologies Advisory Group (RINTAG) was obtained prior to the start of screening.

### Graft entry into study and subsequent preparation

The patient and donor liver pathways can be seen in figure 1. All livers will be retrieved with the intention and standardised technique to use them for transplantation. Following the retrieval procedure at the donor hospital the liver will be placed in ice-cold preservation solution on the back table and transported (according to local protocol). If the liver is allocated to UHBFT, if it is then considered not suitable for use it must be rejected by the on-call transplanting surgeon. For the liver to be considered untransplantable, the liver will be inspected by the on-call transplant surgeon and another transplant surgeon in the department. The liver will then be offered as a fast track graft to the other centres around the UK. If rejected by all centres and if consent for research was taken, it will be considered for use in VITTAL. Livers offered to our unit as fast track offers from other centres will undergo the same two-consultant rejection process. An appropriate consented potential recipient will be selected by the transplant surgeon and contacted by the coordinator and will come into hospital for admission. The coordinator will request three units of packed red blood cells, matched to the intended recipient, for use in the OrganOx metra device. The liver will be prepared according to the procedure for preparing the device for use and placing the organ on the device (described in detail in the OrganOx metra Instructions for Use (IFU) document (V.13.0, 12 March 2016). The liver will be weighed prior to being connected to the device. If cannulation proves impossible, the liver will be rejected as previously intended. If the liver meets the criteria for transplantation, the recipient explantation will commence and the procedure for removing the liver from the device is also described in the IFU. Implantation and reperfusion of the liver will proceed as per the usual practice of the implanting centre. The patient will be clerked as if they were being admitted for a standard liver transplant.

**Figure 1 F1:**
[figure not shown]
Patient and donor liver pathways. HA, hepatic artery; PV, portal vein; UHB, University Hospitals Birmingham; VITTAL, Viability testing and transplantation of marginal livers.

**Table 2 T2:** Trial sample collection schedule

Perfusate samples	Hepatic arterial and hepatic venous biochemistry (point of care)	Preperfusion Every 30 min during perfusion	Cobas point-of-care desktop analyser
	Perfusate supernatant	Preperfusion Every 15 min for first hour Every hour thereafter	5×1 mL aliquots Stored at −80°C
Liver samples	Liver biopsy	L1 Preperfusion L2 After 4 hours L3 at end of perfusion* L4 Postreperfusion	16 G core needle biopsy Divided into segment for formalin, segment for frozen and piece for electron microscopy
	Common bile duct	CBD1 Preperfusion CBD2 Postreperfusion	Formalin
Bile samples	(If produced)	B2 sample at 2 hours B4 sample at 4 hours B6 sample at 6 hours	Total volume recorded and 2 mL samples snap frozen at these time-points
Patient samples	Biochemistry haematology clotting	Visits 1, 2, 3, 4, extended follow-up	Standard of care
	Serum, plasma, mononuclear cells (PBMC)	Visit 1 (preoperative (postinduction of anaesthesia), postreperfusion day 4 postoperative) Visits 2, 3, 4,	Additional research samples
	Urine	Visit 1 (pre-operative [post-induction], postreperfusion Day four post-op)	Additional research samples

*If lasting longer than 6 hours.

PBMC, peripheral blood mononuclear cell.

### Perfusion of the graft

The machine will be primed with a perfusate suitable for NMP-L and will use packed red cells as the oxygen carrier. During the perfusion, biochemical analysis of the blood-based perfusate will be performed using a Cobas biochemical point-of-care analyser (Roche Diagnostics) which will give results for pH, pO_2_, pCO_2_, bicarb, base excess, calcium, chloride, sodium, potassium, haemoglobin, haematocrit, lactate and glucose. Arterial and portal venous flows, resistances and pressures will also be recorded. Samples to be collected are detailed in table 2.

The duration of machine perfusion will be dictated by logistics and the recipient’s explant but should not be less than 4 hours or more than 24 hours. For a graft to be considered for transplantation it must *meet at least 2 of the following criteria* within 4 hours of the start of perfusion:Metabolise lactate to less than or equal to 2.5 mmol/L within 4 hours of the start of the perfusion;
Demonstrate evidence of bile production;Maintain a pH greater than 7.30;Show evidence of glucose metabolism;Maintain stable hepatic arterial flow of more than or equal to 150 mL/min and portal flow more than or equal to 500 mL/min;Achieve homogeneous graft perfusion with soft consistency of the parenchyma.

Once the transplanting surgeon is content that the liver has met the criteria required for transplantation, the recipient will be brought to theatre and the explant will commence.

Explantation, implantation and reperfusion of the liver will be carried out in using standardised techniques by the on-call transplant surgeon. The liver will remain on the machine until after the explantation has taken place at which point it will be flushed by 2 L of cold HTK immediately prior to implantation.

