**Methods and analysis:**

Viability testing and transplantation of marginal livers is an open-label, non-randomised, prospective, single-arm trial designed to determine whether currently unused donor livers can be salvaged and safely transplanted with equivalent outcomes in terms of patient survival. The procured rejected livers must meet predefined criteria that objectively denote their marginal condition. The liver is subjected to NMP-L following a period of static cold storage. Organs metabolising lactate to ≤2.5 mmol/L within 4 hours of the perfusion commencing in combination with two or more of the following parameters—bile production, metabolism of glucose, a hepatic arterial flow rate ≥150 mL/min and a portal venous flow rate ≥500 mL/min, a pH ≥7.30 and/or maintain a homogeneous perfusion—will be considered viable and transplanted into a suitable consented recipient. The coprimary outcome measures are the success rate of NMP-L to produce a transplantable organ and 90-day patient post-transplant survival.

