## Objectives and outcome measures

### Primary

There are two linked primary objectives and respective outcome measures:

Primary objective: (A) Establish the feasibility of NMP-L to increase the number of transplantable livers.

Primary Outcome measure: (A) ‘Rescue rate’ that is, the proportion of rejected livers that can be used for transplantation having been deemed viable following a period of machine perfusion.

Primary objective: (B) Achieve successful transplantation of previously rejected donor livers following viability testing using NMP-L.

Primary outcome measure: (B) 90-day patient survival, calculated as the number of patients alive 90-day post-NMP-L-treated marginal liver transplantation (numerator) divided by the total number of NMP-L-treated marginal liver transplants performed (denominator).

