### Analysis of outcome measures

#### Primary analysis

To assess (A) the feasibility of NMP-L, the rescue rate will be calculated as the number of perfused marginal grafts meeting the criteria for viability (numerator) divided by the total number of perfused marginal grafts (denominator).

$$Rescue\;Rate=\frac{Number\;of\;viable\;perfused\;marginal\;grafts}{Total\;number\;of\;perfused\;marginal\;grafts}$$

To assess (B)—achievement of successful transplantation of previously rejected donor liver following viability testing using NMP-L. We will evaluate 90-day patient survival rate as an indicator of liver function and/or viability following transplantation of marginal liver grafts following NMP-L. The 90-day patient survival rate will be calculated as the number of patients alive at 90-day post-transplant with a VITTAL graft, divided by the total number VITTAL patients transplanted.

$$90\;day\;patient\;survival\;rate=\;\frac{Number\;of\;patients\;alive\;at\;90\;days\;post\;transplantation}{Total\;number\;of\;transplanations\;performed}$$

For (A), all livers undergoing NMP-L treatment will be included for evaluation in the interim and final analyses. For (B), all transplantations performed will be included for evaluation in the interim and final analyses. The rate outcomes will be reported together with confidence intervals using the Wilson (1927) method.^43^

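### The abstract and the Methods state incompatible viability rules: lactate clearance plus two or more other criteria, against any two of six criteria with lactate optional

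*Protocol article*

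**What the plan says.** The rule appears twice in the protocol article.

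- **Abstract, Methods and analysis.** "Organs metabolising lactate to ≤2.5 mmol/L within 4 hours of the perfusion commencing in combination with two or more of the following" parameters are considered viable and transplanted. The parameters that follow are bile production, glucose metabolism, arterial and portal flow, pH and homogeneous perfusion.
- **Methods, Perfusion of the graft.** To be considered for transplantation a graft must "meet at least 2 of the following criteria" within 4 hours. Six items follow: lactate, bile, pH, glucose, flows and homogeneous perfusion. Lactate comes first and is not marked as compulsory.

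The rule is used in three ways:

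- **Co-primary A.** Under Objectives and outcome measures, the rescue rate is "the proportion of rejected livers that can be used for transplantation having been deemed viable following a period of machine perfusion". The Primary analysis section counts in its numerator the perfused grafts that meet the viability criteria.
- **Start of surgery.** Under Graft entry into study and subsequent preparation: "If the liver meets the criteria for transplantation, the recipient explantation will commence". Perfusion of the graft adds the surgeon's agreement: "Once the transplanting surgeon is content that the liver has met the criteria required for transplantation", the recipient goes to theatre.
- **Co-primary B.** The denominator of 90-day survival is the transplants performed, so the rule selects that cohort.

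**The concern.** The two statements differ on substance: whether lactate is compulsory, and how many criteria are needed (two in total, or lactate plus two, which makes three). The abstract is not a shortened form of the Methods. It carries the stricter and more specific rule, while the section where a reader looks for the operative rule carries the looser one.

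Three things are at stake. Co-primary A has two published definitions. Explantation cannot be undone, and the Methods wording would permit it for an organ declined by all UK centres that never cleared lactate. The Discussion also plans to compare livers that fail the criteria with those transplanted, and that comparison needs a single dividing line.

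**Working it through.** **1. The plan's own design for A.** Inputs, from Sample size justification: undesirable rate 0.30, desirable rate 0.50, 24 livers in the first stage, 29 more in the second, stop if fewer than 8 are recovered, success if at least 22 of 53. The text stops below eight and continues above eight; continuing at exactly eight is assumed here.

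P(feasible | p) = Σ (x = 8 to 24) C(24, x) pˣ (1 − p)²⁴⁻ˣ × P(Y ≥ 22 − x), with Y ~ Binomial(29, p).

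- p = 0.30: 0.047, against a stated α of 0.05.
- p = 0.50: 0.902, against a stated power of 0.90.

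The design reproduces. The question is only which livers enter the count.

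**2. The two rules side by side.** Let L = 1 if lactate is cleared in time and 0 if not, and let k be the number of the other five criteria met. Each criterion is read the same way in both places.

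- Abstract: viable if L = 1 and k ≥ 2.
- Methods: viable if L + k ≥ 2.

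| Lactate | Other criteria met | Abstract | Methods |
|---|---|---|---|
| cleared | 2 or more | viable | viable |
| cleared | exactly 1 | not viable | **viable** |
| cleared | 0 | not viable | not viable |
| not cleared | 2 or more | not viable | **viable** |
| not cleared | 0 or 1 | not viable | not viable |

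Two rows disagree. An example of the second is a liver that fails lactate but makes bile and holds pH above 7.30. Read this way, the Methods count is equal to or higher than the abstract count. How much higher depends on the share of livers in those two rows, which the article does not give.

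**3. What one liver can do.** At the final analysis 21/53 = 39.6% fails and 22/53 = 41.5% succeeds. At the interim, 7/24 = 29.2% stops the trial and 8/24 = 33.3% continues under the assumption in step 1. One discordant liver therefore changes the decision, but only when the count lies at the threshold.

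**4. Is there a tie-breaker in the text?** The Preclinical research and pilot study section describes lactate metabolism in combination with bile, pH and flow as predictive of viability. That fits the abstract better, but it gives no count, no threshold and no compulsory item.

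**5. Smaller wording differences.** The abstract has pH ≥7.30 and the Methods pH greater than 7.30. Only the Methods ask for stable flows and for soft tissue ("Achieve homogeneous graft perfusion with soft consistency of the parenchyma"). The Methods apply the 4-hour limit to the whole list, whereas the abstract attaches it to lactate and can be read either way for the rest. The limit needs to be explicit because perfusion may last up to 24 hours and bile is scheduled as "B2 sample at 2 hours B4 sample at 4 hours B6 sample at 6 hours" (Table 2).

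**The case against.** **The list may have lost its structure.** In the text available, a line break follows the lactate item, and that item repeats the 4-hour limit already given in the lead-in. Both would fit a list in which lactate once stood apart. This stands as a possible explanation. It does not remove the contradiction, because the requirement for at least two still precedes lactate, and a restored break would not turn those words into lactate and two others.

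**Figure 1 and the approved protocol are not shown.** The figure's legend defines hepatic artery and portal vein, so the figure may state the criteria. This stands. A reader might infer that the Methods text is the wrong one, or that livers were transplanted on the looser rule. Neither is supported: the preclinical passage favours the abstract only weakly, and nothing here concerns trial conduct.

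**The Methods rule is only a minimum.** The surgeon must also be content, so it permits transplantation without requiring it. That is correct, but it is still a different minimum from the abstract's. It also limits what can be said about a criteria-meeting liver that the surgeon declines: the Primary analysis formula would count it as rescued, while the outcome definition speaks of livers that can be used.

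**The effect may be nil.** In the pilot, five of six livers met the viability criteria (Wilson 95% interval 44% to 97%; the pilot's exact rule is not given). If the true rate were 60% or more, the probability of declaring feasibility would be at least 0.996 and a few discordant livers would not matter. This stands. A reader might also infer an inflated type I error for A. The documents do not support that: the 30% floor is an economic one, not tied to either rule, and at a true 30% under whichever rule operates the error is 0.047.

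**The smaller wording differences are not a rival rule.** A reader might use soft consistency or the time limit to build a liver that passes the abstract and fails the Methods. That treats the abstract's shortening as a deliberate definition, which the text does not justify. These differences need tidying, nothing more.

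**Conclusion.** The point holds as an inconsistency in the published text. The abstract and the Methods differ on whether lactate is compulsory and on the number of criteria, and no text shown reconciles them. Two kinds of liver are classified differently. Because the rule sets the numerator of co-primary A, conditions explantation and selects the cohort for co-primary B, it has to be settled.

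The size of the effect on the rescue rate cannot be determined. What follows from the plan's own thresholds is that one liver is decisive at 21 versus 22 of 53. That the two rules conflict is certain as the text stands; which of them is operative is not. The conclusion assumes that the Methods list is complete as shown.

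**What to change.** First confirm the operative rule in the approved protocol and figure 1. Then state it in identical terms in the abstract and under Perfusion of the graft. Unless those sources say otherwise, the stricter rule is the safer default and fits the preclinical rationale: lactate ≤2.5 mmol/L within 4 hours AND two or more of the remaining five criteria. Use one wording each for pH, flows and tissue consistency, and one time limit that says which criteria it covers.

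If the approved protocol does carry the any-two rule, report the rescue rate under both rules and identify any transplanted liver that did not clear lactate. The perfusion form described under Electronic case report forms collects perfusion parameters, biochemistry and perfusion outcome, so this should need no new data.

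Cost: one sentence in the Methods and matching wording in the abstract. No extra visits and no change to the sample size or stopping boundaries.
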